## Abstract

**Background:**

Diabetes model projects in different regions of Germany including interventions such as quality circles, patient education and documentation of medical findings have shown improvements of HbA1c levels, blood pressure and occurrence of hypoglycaemia in before-after studies (without control group). In 2002 the German Ministry of Health defined legal regulations for the introduction of nationwide disease management programs (DMP) to improve the quality of care in chronically ill patients. In April 2003 the first DMP for patients with type 2 diabetes was accredited. The evaluation of the DMP is essential and has been made obligatory in Germany by the Fifth Book of Social Code. The aim of the study is to assess the effectiveness of DMP by example of type 2 diabetes in the primary care setting of two German federal states (Rheinland-Pfalz and Sachsen-Anhalt).

**Methods/Design:**

The study is three-armed: a prospective cluster-randomized comparison of two interventions (DMP 1 and DMP 2) against routine care without DMP as control group. In the DMP group 1 the patients are treated according to the current situation within the German-Diabetes-DMP. The DMP group 2 represents diabetic care within ideally implemented DMP providing additional interventions (e.g. quality circles, outreach visits). According to a sample size calculation a sample size of 200 GPs (each GP including 20 patients) will be required for the comparison of DMP 1 and DMP 2 considering possible drop-outs. For the comparison with routine care 4000 patients identified by diabetic tracer medication and age (> 50 years) will be analyzed.

**Discussion:**

This study will evaluate the effectiveness of the German Diabetes-DMP compared to a Diabetes-DMP providing additional interventions and routine care in the primary care setting of two different German federal states.

## Background

Diabetes is a major and growing health care problem. The number of diabetes patients is expected to increase globally from 135 to 300 million between 1995 and 2025 [1], the vast majority will have type 2 diabetes [2]. The quality of care for diabetic patients in Germany was like in many western countries criticized for more than two decades. The Expert Committee of the Government therefore recommended in 2003 diabetes as a priority area [3]. Epidemiological data from primary care was mostly lacking, although recently published data showed that performance of practices and diabetes control in patients could be better than suggested [4-6]. Quality of care is expected to improve within disease management programs (DMP) by the implementation of evidence-based clinical practice, by means of guidelines, quality circles, educational meetings, outreach visits, patient education and by improving coordination among different health care providers [7,8]. Consequently, clinical guidelines and DMPs for primary care have been developed to improve quality and cost-effectiveness of health care for chronic conditions such as diabetes.

In the reform law of 2002 the German Ministry of Health defined a complicated process for the introduction of DMPs and on 27 February 2003 the Federal Insurance Office accredited the first DMP for type 2 diabetes [9]. Several patient- and provider-oriented interventions within the German-style DMP aiming at decreasing mortality and morbidity of patients with type 2 diabetes reducing micro- and macrovascular complications and increasing quality of life of diabetes patients. The underlying criteria therefore have been developed by the newly formed Coordinating Committee and have gone through a tough process of certification before they have been regulated by law by the Ministry of Health in 2002 [10]. The German DMP structure is tightly linked to financial incentives for the sickness funds, i.e. it is linked with the risk structure compensation (= RSC) which was introduced to compensate for differences in the risk structure of the insured population. [9]. Besides the requirement of a comprehensive documentation and the obligation to provide guideline-oriented healthcare the statutory health insurances are obliged to evaluate DMPs by the Fifth Book of Social Code [9,11].

However, until now valid scientific data showing the effectiveness of the German Diabetes-DMP are missing. Recently published data of diabetes model projects in the region of Nordrhein, Sachsen-Anhalt and Baden-Wuerttemberg show improvements of HbA1c levels, blood pressure and occurrence of hypoglycaemia [12-14]. However, the duration of these model projects was too short to draw conclusions concerning clinical endpoints (i.e. a cardiovascular events, amputation rate) and bias because of the preferred inclusion of highly motivated patients can not be excluded [15].

## Methods/Design

### Aim and design of the study

The aim of the study is to assess the effectiveness of DMP compared to routine care in the primary care setting of two different German federal states (Rheinland-Pfalz and Sachsen-Anhalt). Since DMPs are liable to an implementation process ongoing at the moment which is differing considerably depending on several criteria (e.g. region of Germany, rural/urban area, health insurance) three groups will be observed: a "routine care group without DMP" (= control group; CG), a "DMP real group" (= DMP 1) and a group of patients participating in an (within the scope of the German law regulations) optimally in practices implemented DMP (= DMP 2).

The study is designed as a prospective cluster-randomized comparison of the two intervention groups (DMP 1 and DMP 2) against routine care as control group (Fig 1). The cluster randomization was chosen because this has optimal internal validity (absence of confounders) while avoiding contamination of interventions associated with patient randomisation.

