### Scientific hypotheses

• The German-Diabetes-DMP (DMP 1) is more effective than routine diabetes care (CG)

• An optimally implemented form of the Diabetes-DMP (DMP 2) is more effective than the German-Diabetes-DMP (DMP 1).

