#### Selection of participants

500 GPs in Rheinland-Pfalz and 500 GPs in Sachsen-Anhalt participating in the Diabetes-DMP will be recruited by an invitation letter giving information about the study project. From those who will accept to participate, 100 GPs will be randomized in the DMP group 1 and 100 in the DMP group 2. All patients with a type 2 diabetes out of these practices insured at the general regional health funds (*Allgemeine Ortskrankenkassen = AOK*) and participating in the DMP will be included in the study then. Incomplete participation in the interventions will be an exclusion criterion in the DMP group 2.

For the control group 4000 AOK patients out of practices not participating in the DMP will be detected through diabetes tracer medication and age (> 50 years) and will be matched. Participation in a DMP offered by another health fund is an exclusion criterion in the control group.

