#### Outcome-parameter

Outcome parameters were defined considering best available evidence, legal regulations and feasibility. According to our two scientific hypotheses two groups of outcome parameters were defined: "outcome parameters I" for the comparison of the DMP groups and "outcome parameters II" for the comparison of DMP and routine care. This differentiation of the outcome parameters is essential because in the control group availability of patient data will be limited to process indicators only. The outcome parameters are displayed in Table 1.

**Table 1 T1:** Primary and secondary outcome parameters

**OUTCOME PARAMETERS I**	**OUTCOME PARAMETERS II**
**DMP 1 vs. DMP 2**	**DMP 1 vs. CG**
***Primary outcome parameter***	***Primary outcome parameter***

Proportion of patients achieving target values for HbA1c and RR according to the legal regulations (10)	Proportion of patients with prescriptions for antidiabetic, antihypertensive and lipid-lowering drugs

***Secondary outcome parameters***	***Secondary outcome parameters***

Proportion of patients with prescriptions for antidiabetic, antihypertensive and lipid-lowering drugs	----
Proportion of patients with referrals to ophthalmologists, specialists for diabetology and diabetic feet	Proportion of patients with referrals to ophthalmologists, specialists for diabetology and diabetic feet
Proportion of patients referred to a patient education training for diabetes and hypertension	Proportion of patients referred to a patient education training for diabetes and hypertension
Proportion of patients with severe complications (amputation, dialysis etc.)	Proportion of patients with severe complications (amputation, dialysis etc.)
Proportion of patients with > 2 hospitalizations in the last 6 months	Proportion of patients with > 2 hospitalizations in the last 6 months
Consultation rate	Consultation rate
Days of incapacity to work	Days of incapacity to work
Mean differences of HbA1c, RR, BMI and glomerular filtration rate	---
SCORE risk chart (RR, cholesterol, smoking status, age, gender)	---
Drop out rate from the DMP	---

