## Discussion

There are specific difficulties in evaluating the effectiveness of complex interventions such as disease management programs [19], particularly, in our case that implementation process has already started [15]. At the moment it is not conceivable to which phase of the implementation process the DMP actually has preceded. However, the DMP group 2 represents an ideal implementation of the DMP within the scope of the German law regulation.

To adapt the evaluation design to the real conditions of diabetes care in Germany at the moment, but also to consider the ongoing implementation process we have chosen the design of a prospective randomized-controlled comparison of the two DMP groups embedded in the quasi-experimental design of a controlled before-after study with a blinded control group. The quasi-experimental design is predetermined because allocation to the control group can not be perfomed randomly and because baseline values for patients participating in the DMP have not been documented.

A fully experimental design with a randomized control group was rejected by the authors, because this could create an artificial care situation. That is informing patients and GPs of the control group about the study and probably asking for completing any questionnaires would introduce an enormous bias.

According to the theoretical model for design and evaluation of complex interventions by Campbell et al the presented study can be assigned to phase III and IV (15, 20). However, pilot projects have shown that an observation period of 24 months will be too short to show significant differences in severe clinical endpoints (i.e. amputations, diabetic renal insufficiency, cardio-vascular events). Therefore it was decided to have a combination of HbA1c and blood pressure as primary endpoint in the randomized part of the trail and prescriptions in the quasi-experimental part of the trial.

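### The comparison with routine care is labelled cluster-randomised and free of confounders, but only DMP 1 versus DMP 2 is randomised, so Hypothesis 1 cannot carry a randomised effectiveness conclusion

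*Protocol article*

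**What the plan says.** **Label.** The Methods/Design paragraph of the Abstract calls the study "a prospective cluster-randomized comparison of two interventions (DMP 1 and DMP 2) against routine care without DMP as control group". The section on aim and design of the study repeats this in the body: it is "designed as a prospective cluster-randomized comparison of the two intervention groups (DMP 1 and DMP 2) against routine care as control group". The next sentence there gives the reason: "The cluster randomization was chosen because this has optimal internal validity (absence of confounders", together with the avoidance of contamination.

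**Allocation.** Under selection of participants, "100 GPs will be randomized in the DMP group 1 and 100 in the DMP group 2". The same section then describes the control group separately: 4000 AOK patients from practices outside the DMP, found through tracer drugs and an age above 50, and matched. The Discussion states that "allocation to the control group can not be perfomed randomly" and describes a randomised comparison of the two DMP groups placed inside a quasi-experimental, controlled before-after study.

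**Aim and hypothesis.** The aim is effectiveness of the DMP relative to routine care. The first scientific hypothesis (Hypothesis 1 here) reads "The German-Diabetes-DMP (DMP 1) is more effective than routine diabetes care (CG", with no qualification.

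**Outcomes.** The section on outcome parameters says that "in the control group availability of patient data will be limited to process indicators only". Table 1 makes prescribing the primary outcome for DMP 1 versus control.

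**The concern.** The label and the allocation cannot both be true of the routine-care contrast. The Abstract and the aim-and-design section attach randomisation to the comparison with routine care. The selection section and the Discussion show that randomisation operates only between the two DMP groups.

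This touches the main aim. The question of whether the DMP beats routine care is answered by the non-randomised contrast, and its hypothesis is phrased as a plain claim of effectiveness. Someone who takes the design statement at its word would give a difference in prescribing between DMP 1 and control the weight of trial evidence. They would see no need to ask how the two groups of practices and patients came to differ before the study began.

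A second, smaller conflict sits beside it. One sentence limits control data to process indicators, while Table 1 lists for the same comparison several outcomes that go beyond process. A reader cannot tell what kind of evidence Hypothesis 1 will rest on.

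**Working it through.** The plan gives no figure for this point that could be reproduced. Its sample size concerns DMP 1 versus DMP 2 and is not disputed here. The check is a count of what is randomised, followed by a comparison of the statements.

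**1. What is randomised (selection of participants; sample size calculation)**

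- GPs randomised: 100 + 100 = 200, all of them already in the DMP.
- Planned patients under these GPs: 200 × 20 = 4000, or 2000 in each DMP group.
- GPs randomised to routine care: 0.
- Control patients present by randomisation: 0 of 4000.

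**2. Statements side by side**

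| Contrast | Abstract; aim and design | Selection of participants; Discussion |
|---|---|---|
| DMP 1 vs DMP 2 | cluster-randomised | GPs randomised: consistent |
| DMP 1 vs routine care | cluster-randomised | matched, not randomised, quasi-experimental: contradictory |
| Absence of confounders | aim and design only; follows directly on the sentence that names routine care | supportable as an aim for DMP 1 vs DMP 2 only |

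**3. How DMP 1 and control come to differ, from the document alone**

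- *Practice:* DMP 1 practices take part in the programme; control practices do not.
- *GP:* 500 + 500 = 1000 GPs are invited and 200 are to be randomised, so the randomised GPs are 200/1000 = 20% of those invited. They give a written declaration of willingness (timeframe section). Control GPs are neither invited nor informed.
- *Patient:* DMP participation is voluntary (ethics section). The Background raises the selection of motivated patients as a weakness of earlier model projects.
- *Identification:* controls are found by tracer drugs and age. The text states no such condition for DMP patients, who enter through their diagnosis and enrolment. Since antidiabetic prescribing is part of the primary outcome, the groups are selected differently on something close to what is measured. Bias could therefore run in either direction.

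Matching can reduce imbalance in the factors matched on. It does not create the property that randomisation gives. The before-after element does not clearly supply it either, because the Discussion says that baseline values of DMP patients have not been documented.

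**4. What Hypothesis 1 measures (Table 1)**

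The primary outcome is the proportion of patients with prescriptions for three drug groups, which is a process measure. Control of HbA1c and blood pressure, the primary outcome for DMP 1 versus DMP 2, is not listed for the comparison with control.

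**5. Process indicators against Table 1**

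For DMP 1 versus control, Table 1 also lists severe complications, patients with more than two hospitalisations, and days of incapacity to work. These three entries do not fit a restriction to process indicators.

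**The case against.** The best reply is that the document knows what it is doing. The Discussion names the quasi-experimental design, explains why a randomised control group was rejected, and assigns prescribing to that part of the study. The selection section describes the controls separately and plans matching, and even the Abstract says that they are found by tracer drugs and age. The no-confounders phrase, set beside contamination, can be read as concerning only the choice to randomise GPs. Hypothesis 1 is given practical meaning through a stated process outcome, with reasons.

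Most of this stands, and it limits the point. Several stronger readings are tempting, and the document does not support them:

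- *That the design is concealed.* It is disclosed in the Discussion.
- *That the Abstract also claims absence of confounders.* Only the aim-and-design section does.
- *That control practices refused the DMP.* The text says only that they do not take part.
- *That the bias has a known size.* Nothing in the document supplies one. Assume a 50% rate, no true effect, 2000 DMP 1 patients, 4000 controls and a design effect of 1 + 19 × 0.05 = 1.95. The standard error is √(0.25 × 1.95/2000 + 0.25/4000) = 1.75 points if only DMP 1 is inflated, and √(0.25 × 1.95/2000 + 0.25 × 1.95/4000) = 1.91 points if both groups are. An assumed residual imbalance of 1, 2, 3, 5 or 10 points would then be declared significant with probability 0.08–0.09, 0.18–0.21, 0.35–0.40, 0.74–0.82 or above 0.99. The answer follows the assumption, so the point does not rest on it.
- *That Hypothesis 1 cannot be studied at all.* An adjusted association can still be reported.

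What the reply does not remove is the literal text. Two sentences attach cluster randomisation to routine care, and the statement on confounders follows directly on one of them. A correct account in the Discussion does not correct the design statement.

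**Conclusion.** The contradiction is real and concerns the study's main aim. Two design statements, in the Abstract and in the aim-and-design section, credit the routine-care comparison with cluster randomisation. One of them is followed by a claim that confounders are absent. By the document's own account no GP is randomised to routine care and 0 of 4000 controls are randomised. Hypothesis 1, one of two, therefore rests on a matched quasi-experimental contrast with prescribing as its primary outcome, and cannot carry a randomised conclusion on effectiveness. DMP 1 versus DMP 2 is unaffected.

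This rests on the text alone and needs no numerical assumption. The size and direction of any bias are unknown. The conflict between the process-indicator sentence and Table 1 is also real but secondary. How matching and adjustment are to be done may stand in a fuller document and is not faulted here.

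**What to change.** 1. In the Abstract and in the aim-and-design section, apply the cluster-randomised label to DMP 1 versus DMP 2 only.
2. In the aim-and-design section, confine the statement on absence of confounders to that same comparison.
3. In both places, describe DMP 1 versus control as a matched quasi-experimental comparison, in line with the Discussion.
4. Restate Hypothesis 1 as an adjusted, non-randomised difference in prescribing and process of care between DMP 1 and routine care.
5. Reconcile the sentence that limits control data to process indicators with the complications, hospitalisations and incapacity days that Table 1 lists for DMP 1 versus control.

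The cost is a few sentences. No new data, sample size or randomisation is needed. The real price is that the headline claim for Hypothesis 1 becomes weaker. A further AOK extract from DMP practices outside the study could be considered as a check on volunteer effects among GPs. It is optional, because it leaves the larger difference between DMP and non-DMP practices and patients untouched.

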**Figure 1 F1:**
[figure not shown]
Study design.

### Scientific hypotheses

• The German-Diabetes-DMP (DMP 1) is more effective than routine diabetes care (CG)

• An optimally implemented form of the Diabetes-DMP (DMP 2) is more effective than the German-Diabetes-DMP (DMP 1).

#### Sample size calculation

Sample size calculations for cluster randomized trials differ from sample size calculations for common RCTs requiring a larger number of patients. Based on the main outcome parameters we performed a power calculation with the Cluster Randomization Sample Size Calculator ver.1.02 of the University of Aberdeen on the basis of an ICC of 0,05. Considering possible drop-outs a sample size of 200 GPs will be required (each GP including 20 patients).

#### Selection of participants

500 GPs in Rheinland-Pfalz and 500 GPs in Sachsen-Anhalt participating in the Diabetes-DMP will be recruited by an invitation letter giving information about the study project. From those who will accept to participate, 100 GPs will be randomized in the DMP group 1 and 100 in the DMP group 2. All patients with a type 2 diabetes out of these practices insured at the general regional health funds (*Allgemeine Ortskrankenkassen = AOK*) and participating in the DMP will be included in the study then. Incomplete participation in the interventions will be an exclusion criterion in the DMP group 2.

For the control group 4000 AOK patients out of practices not participating in the DMP will be detected through diabetes tracer medication and age (> 50 years) and will be matched. Participation in a DMP offered by another health fund is an exclusion criterion in the control group.

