### Intervention

The minimum requirements for the Diabetes-DMP are regulated by law and defined in the RSAV [10]. According to the legal regulations the intervention in the DMP1 group comprises consultations at 3- or 6-months intervals. During these consultations a detailed diabetes-specific anamnesis and physical examination incl. taking blood pressure and an analysis of HbA1c are carried out. Furthermore agreements are made concerning further treatment, e.g. target values for HbA1c and blood pressure and participation on patient education programs for diabetes or hypertension. All medical findings as well as the current medication have to be documented within structured, standardized documentation sheets at each consultation. If required a referral to a specialist (e.g. ophthalmologist) will be arranged. Furthermore the GPs get a special diabetes-handbook including current, evidence-based information about diabetes therapy. The GPs participating in the DMP1 group will receive no additional intervention.

There are major difficulties introducing new evidence into general practice requiring comprehensive implementation support at different levels (patients, doctors, practice team) [17,18]. Therefore, in the DMP 2 group implementation support at the level of doctors and practice team will be provided. In addition to the clinical interventions at patients level in the DMP group 1 several components aiming at optimizing the implementation process are provided in this group (= implementation interventions) (Table 2).

**Table 2 T2:** Implementation Interventions in DMP 2 group

**Interventions**	**Description**
Interactive quality circle meetings	During these meetings all aspects of evidence based treatment of diabetes in a primary care setting will be discussed (2 × per year).
Educational meetings for medical assistants	During these meetings medical assistants will be supported in finding individual strategies for optimal implementation of the DMP in their practices (2 × per year).
Outreach visits	During these meetings individual problems within the implementation process of the DMP will be discussed with the GP and the assistant team (1 × per year)
Homepage with "best practice" examples	Detailed information for the praxis team about Diabetes-DMP incl. case studies via internet (electronic individual feedback)

The control group represents routine care without DMP. There will be no intervention at all.

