### Timeframe of the study

The study team will start to invite GPs at the end of September 2005. After receiving a written declaration of their willingness to participate in the study and to accept random assignment to the different groups GPs will be randomized.

Patient inclusion and pre-data collection will start in 2005. The observation period will be 24 months.

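### GPs are randomised, but patients are taken from practices and DMP 2 is directed at practice teams, so GPs who share a practice could be split between the arms

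*Protocol article*

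**What the plan says.** The protocol article uses two units for the randomised comparison of DMP 1 with DMP 2.

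- **Allocation is by GP.** Selection of participants: "100 GPs will be randomized in the DMP group 1 and 100 in the DMP group 2". Timeframe of the study repeats it: once they agree "to accept random assignment to the different groups GPs will be randomized".
- **Sample size is by GP.** Sample size calculation gives 200 GPs with 20 patients each, an ICC of 0.05, and drop-outs taken into account.
- **Patient inclusion is by practice.** The sentence after the allocation rule takes "All patients with a type 2 diabetes out of these practices insured at the general regional health funds" who are also in the DMP.
- **DMP 2 acts on the practice.** Intervention: "in the DMP 2 group implementation support at the level of doctors and practice team will be provided". In Table 2, "medical assistants will be supported in finding individual strategies for optimal implementation of the DMP in their practices", and at the outreach visits "individual problems within the implementation process of the DMP will be discussed with the GP and the assistant team". The homepage is also meant for the practice team.
- **DMP 1 GPs get nothing extra** (Intervention).

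Aim and design of the study gives, as one reason for cluster randomisation, "avoiding contamination of interventions associated with patient randomisation".

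**The concern.** When an intervention trains a team, cluster randomisation protects the comparison only if the team stays whole within one arm. The article does not limit enrolment to one GP per practice, does not keep colleagues in one arm, and does not define GP and practice as the same thing. Followed literally, the rule allows two GPs with the same assistants to be allocated apart.

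Two things would follow in such a practice. First, assistants supported for DMP 2 would also look after the DMP 1 colleague's patients. Second, because patients enter through the practice, they would qualify under both GPs and their arm would not be defined. The second problem arises even without spill-over.

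At stake is the only randomised contrast in the study, with its primary outcome of reaching the HbA1c and blood pressure targets (Table 1). Contamination would pull that contrast toward no difference, and an intention-to-treat analysis would not undo it.

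**Working it through.** **Inputs from the article:** 100 GPs per arm, 20 patients per GP, ICC 0.05.

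**Assumed, because the article does not give them:** two-sided 0.05, 80% power, a DMP 1 success rate of 50%, all 200 GPs analysed, the share *s* of GPs in two-GP practices where both are randomised, and the degree of spill-over *c* (0.5 or 1).

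**1. The planned size.** Design effect = 1 + (20 − 1) × 0.05 = 1.95. Effective patients per arm = 2000/1.95 = 1026. SE of the difference = √(2 × 0.25 × 1.95/2000) = 2.2 percentage points. The difference detectable with 80% power is 2.80 × 2.2 ≈ 6.2 points. The figure of 200 GPs is plausible but cannot be reproduced uniquely. For example, 50% versus 57% with 80% power and 20% drop-out gives 195 GPs, and 50% versus 58% with 90% power and 20% drop-out gives 200. Nothing below disputes the 200.

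**2. Chance of a split.** Once one GP of a pair has been placed, 100 of the remaining 199 places are in the other arm: 100/199 = 50.3%.

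**3. Share of DMP 1 GPs affected.** Pairs = 200*s*/2, and split pairs = pairs × 100/199. Each split pair puts one GP into DMP 1. With *s* = 10% there are 10 pairs and about 5 splits, so about 5 of 100 DMP 1 GPs. With *s* = 20% there are 20 pairs and about 10 splits, so about 10 of 100.

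**4. Power.** The expected difference shrinks by the factor 1 − *q*, where *q* = (share affected) × *c*. Power ≈ Φ((1 − *q*) × 2.80 − 1.96).

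| GPs in randomised pairs | DMP 1 GPs affected | Power, half spill-over | Power, full spill-over |
|---|---|---|---|
| 0% | 0 | 80% | 80% |
| 10% | about 5 | 78% | 76% |
| 20% | about 10 | 76% | 71% |

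**5. Cost of randomising whole practices.** A two-GP practice becomes a cluster of 40 patients with design effect 1 + 39 × 0.05 = 2.95 (same ICC assumed). Effective patients per arm = 100 × [(1 − *s*) × 20/1.95 + (*s*/2) × 40/2.95]. This is 991 at *s* = 10% and 956 at *s* = 20%. To recover 1026 takes 200 × 1026/991 ≈ 207.02, rounded up to 208 GPs, and 200 × 1026/956 ≈ 214.5, rounded up to 215 GPs. With one GP per practice the number stays at 200.

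**The case against.** The strongest reply is that the article may simply mean one GP per practice. The reference to practices follows directly on the 200 randomised GPs, the outreach visit is described with a single GP and the assistant team, and each GP is said to include 20 patients. A one-GP rule, or joint allocation of colleagues, could also stand in the full protocol, which a journal article condenses. This stands in part: no section shows that any practice contributes two GPs. It does not make the printed rule sound, because that rule names the GP as the unit allocated while inclusion and intervention work through the practice.

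Three stronger inferences are tempting, and the article does not support them.

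- **That the design contradicts its own rationale.** The article claims to avoid contamination only relative to patient randomisation, and that remains true with the GP as unit. The protection is incomplete if practices are shared, but there is no self-contradiction.
- **That the DMP 2 effect is diluted and the sample size is clustered at the wrong level.** Both hold only if colleagues from one practice are both enrolled, which the article does not say.
- **That the power loss is large.** If 20% of DMP 1 patients were fully exposed, power would be 61%. That requires about 40% of all GPs to be in randomised pairs (0.20 ÷ 0.5025 ≈ 0.40) and every exposed patient to receive the whole DMP 2 effect. Full spill-over is an upper limit: the quality circles are listed separately from the assistants' meetings and the visits, and a DMP 1 colleague would not automatically receive them.

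It is also fair to say that contamination of this kind works against finding a benefit of DMP 2. It would not create a false one.

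**Conclusion.** The point holds as a conditional weakness in a stated rule. If two participating GPs share a practice, the article's allocation would separate them about half the time. One team would then work in both arms, the arm of the practice's patients would be unclear, and the randomised difference would be biased toward none.

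The size is unknown and may be zero, because the number of practices with more than one participating GP is not given. With 10 to 20% of GPs in such pairs, power would fall from an assumed 80% to 76–78% with half spill-over or 71–76% with full spill-over. These figures illustrate assumed inputs and do not estimate what happened in this trial. The point is still worth acting on, because a split practice cannot be put back together after allocation.

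**What to change.** Before randomisation, do one of the following and state it in the selection section.

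- **Randomise practices.** All participating GPs of one practice go to the same arm, and the practice is the cluster in the sample size and the analysis. The cost is slightly fewer or larger clusters: for the same information, about 208 GPs if 10% are in two-GP practices and about 215 if 20% are (same ICC assumed). The plan invites 1000 GPs (500 in each state).
- **Enrol one GP per practice.** The 200 GPs stay unchanged. The text should then say that the GP and the practice are the same cluster.

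If one of these rules already applies, one sentence saying so settles the point.
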